## Abstract

**Background:** Falls are the leading cause of fatal and non-fatal injuries among older adults. Perturbation-Based-Balance Training (PBBT) is a promising approach to reduce fall rates by improving reactive balance responses. PBBT programs are designed for older adults who are able to stand and walk on a motorized treadmill independently. However, frail older adults, whose fall rates are higher, may not have this ability and they cannot participate. Thus, there is a critical need for innovative perturbation exercise programs to improve reactive balance and reduce the fall risks among older adults in a wider range of functioning. Trunk and arms are highly involved in reactive balance reactions. We aim to investigate whether an alternative PBBT program that provides perturbations during hands-free bicycling in a sitting position, geared to improve trunk and arm reactive responses, can be transferred to reduce fall risks and improve balance function among pre-frail older adults.

**Methods:** In a single-blinded randomized-controlled trial, 68 community-dwelling pre-frail older adults are randomly allocated into two intervention groups. The experimental group receives 24-PBBT sessions over 12-weeks that include self-induced internal and machine-induced external unannounced perturbations of balance during hands-free pedaling on a bicycle-simulator system, in combination with cognitive dual-tasks. The control group receives 24 pedaling sessions over 12-weeks by the same bicycle-simulator system under the same cognitive dual-tasks, but without balance perturbations. Participants' reactive and proactive balance functions and gait function are assessed before and after the 12-week intervention period (e.g., balance reactive responses and strategies, voluntary step execution test, postural stability in upright standing, Berg Balance Test, Six-meter walk test, as well as late life function and fear of falling questionnaires).

**Discussion:** This research addresses two key issues in relation to balance re-training: (1) generalization of balance skills acquired through exposure to postural perturbations in a sitting position investigating the ability of pre-frail older adults to improve reactive and proactive balance responses in standing and walking, and (2) the individualization of perturbation training to older adults' neuromotor capacities in order to optimize training responses and their applicability to real-life challenges.

**Clinical Trial Registration:**
www.clinicaltrials.gov, NCT03636672 / BARZI0104; Registered: July 22, 2018; Enrolment of the first participant March: 1, 2019. See Supplementary File.

## Introduction

Older adults' falls and fall-related injuries are serious and costly health problems. Falls are the leading cause of fatal and nonfatal injuries, and it is reported that between 30 and 40% of community-dwelling older persons fall at least once a year (1). Of those who fall, about 30% suffer moderate-to-severe injuries that reduce mobility and decrease independence, and are responsible for 70% of accidental deaths in persons aged 75 and older (2, 3). Ninety-five percent of hip fractures are caused by sideways falls (1, 3) and result from pure medio-lateral balance control. The psychological impact of a fall often results in a self-restricting decrease in activities, along with a decrease in quality of life (4). Apart from the personal suffering, falls constitute a high cost for public healthcare systems worldwide (5). In the US in 2014, the average costs of fatal and non-fatal falls were $26,340 and $9,780, respectively. The estimated direct medical cost for fall-related injuries was $31.3 billion (6).

Balance is an important foundation for independent daily functioning (3, 7, 8), and is a major training component in fall prevention programs (1–4, 9). Ineffective balance compensatory (reactive) reactions following an external-induced unexpected loss of balance such as a push, slip, or trip is one of the major causes of falls in older adults (9). Unexpected loss-of-balance situations trigger reactive balance responses which act to restore equilibrium, these responses depend on the size, type, and direction of the perturbation (10–12). Fixed base-of-support (BoS) strategies (feet remaining in place) are used to restore balance with ankle, hip, trunk, and arm movements during minor-to-moderate unexpected perturbation magnitudes, whereas at larger balance perturbations, change of BoS strategies such as a stepping response are used (9). When balance is unexpectedly lost, a quick reactive step can prevent a fall from occurring (9); however, it was also found that hip, trunk, and arm movements are also part of reactive stepping reactions (9, 12–15). A recent laboratory study of 83 older adults with varying histories of falls who were exposed to a wide range of perturbation magnitudes found that about 61% of these resulted in fixed BoS balance reactions without the need to recover balance by stepping (15). In fact, by using hip, trunk, and arm movements, the older adults were able to decelerate the center of mass (CoM) movement over the BoS, which may result in an ability to perform balance recovery steps at a higher perturbation magnitude, i.e., higher step threshold. A low step threshold was previously shown to be an independent predictor of a future fall (16–21).

Perturbation-based balance training (PBBT), where participants experience repeated postural perturbations during standing or walking in a safe and controlled environment, is a relatively novel approach of fall-prevention exercise that aims to specifically improve reactive balance control in situations where balance is lost unimpededly (22–25). Unlike conventional forms of balance exercise, only a few repetitions of PBBT led to lasting improvements (i.e., 6–12 months) in reactive balance control (26) and even prevented falls in daily life (27). Other studies also demonstrated that older adults who participated in PBBT programs could adapt in a reactive and proactive manner (22, 27–29). Mansfield et al. (22) reported 46% fewer falls than those in the control groups and showed a reduction in diverse risks of falls (22–29) and their incident rate (22–24).

PBBT exercise programs use different mechatronic systems that provide external perturbations in various ways during standing and walking positions. These intervention programs and devices are designed to specifically train the change of BoS strategies (i.e., reactive stepping or grasp reactions) in older adults who are able to stand or walk independently without external support i.e., without holding the handlebars, lasting in a range of 20–45 min each (22–29). Because of the difficulty of the PBBT approach, it may not match frail older adults or people in pre-walking phases of rehabilitative in neurological patients. Therefore, these populations cannot gain from the PBBT that has been conducted to date. In order to match the PBBT approach to a wider range of older adults and patient populations, we aimed to design an alternative PBBT program that uses a new technology that provides unexpected perturbations while sitting, thus, focusing on training reactive and proactive hip, trunk, and arm reactive movements. We were also inspired by recent works that found that older adults who bicycle outdoors regularly have better balance control than aged-match controls (30, 31), and the amount of outdoor bicycling was associated with better balance control (32).

Bicycle training is beneficial for people suffering from heart disease (33), Parkinson's disease (34), and diabetes (35), and it reduces cholesterol, hypertension, and body fat (36), increases muscle power and endurance (36), improves gait parameters (34), executive function (34, 35), and quality of life (33) in older adults. However, using a stationary bicycle as a means of balance control and fall prevention for this population has been found ineffective (37–39). This is not surprising since stationary bicycling does not specifically train balance skills. However, we wondered if the health advantages of bicycling could be combined with the PBBT principals to create a perturbation-based bicycling training program aimed specifically to challenge trunk and arm reactive responses and proactive balance movements in a sitting position to improve reactive and proactive balance in standing and walking in older adults.

In this study we aimed to investigate a new PBBT method and program and to determine whether 12-weeks perturbation-based bicycling training can improve reactive and proactive balance in standing and walking and reduce fall risk in pre-frail older adults, because age-related deterioration of balance function that leads to an increased risk of falling affects all older adults.

A new PBBT method called the Perturbation Stationary Bicycle Robotics (PerStBiRo) system was developed especially for this novel training program (Figure 1). The PerStBiRo system is composed of a stationary training bicycle mounted on a moving platform and a motor that provides unexpected medio-lateral (ML) tilting perturbations during hands-free bicycling, aiming specifically to improve reactive and proactive trunk and arm balance reactions. Perturbations are provided in two forms, “internal” and external balance perturbations. The internal perturbations are self-induced and provided by the unfixed and unstable mode of the moving platform, i.e., the platform is “floating” and subjected to the forces exerted on it by the trainee during pedaling (Figure 1A). These situations fall under proactive balance control training. The external perturbations are machine-induced programmed and are provided unexpectedly during bicycling (Figure 1B). These situations fall under reactive balance control training. Our training program, with the help of the PerStBiRo system, is built on a gradual increase in difficulty of several exercise components with respect to motor learning, strength endurance, and especially balance control, such as increasing perturbation magnitudes, varied practice in a block or random perturbation order, and two external cue types (visual or sensorimotor) that are provided to better implement motor learning of balance control and improve the trainee's internal sensorimotor feedback (38). During training, concurrent cognitive visual tasks are provided to distract the participant, thus, facilitating implicit learning and automatization, similar to everyday situations where balance is lost unexpectedly.

**Figure 1 F1:**
[figure not shown]
Photos of the PerStBiRo system. The system provides Medio-Lateral tilting perturbations in two ways: self-induced internal **(A)** and external machine-induced **(B)** perturbations. **(A)** Represent a self-induced 'internal' balance perturbation, while the trainee keeps balance when the motor is released, and the moving platform is “floating” during pedaling. **(B)** Represent an external machine-induced programmed balance perturbation during bicycling. The PerStBiRo system is composed of a stationary training bicycle mounted on a moving platform, servo-motor, motor's motion control system, gear mechanism, motion capture system (Microsoft Kinect^KM^ system), safety harness, TV screen and a trainer station with the host PC. The host PC consists the main computer program and serves as a user interface for creating training programs, running them, monitoring upper body movements in real time and analyzing the post-session balance responses.

We hypothesize that older adults will generalize and transfer the learned reactive trunk and arm movements that will be consistently trained during perturbation-based bicycling training in a sitting position into balance control performances in standing and walking. This research addresses a key question about the generalizability of balance rehabilitation and the underlying locomotor plasticity of older adults using perturbation-based bicycling training as an innovative approach, and the degree to which a perturbation-based bicycling training protocol transfers to laboratory losses of balance—a crucial aspect in clinical application.

## Methods and Analysis

This is a parallel single-blinded randomized-controlled trial (RCT) that follows the recommendations of SPIRIT 2013 (see Table 1 for the study flow diagram). Older adults are randomly assigned to one of two groups: (1) Perturbation Training during hands-free Stationary Bicycling Riding (PerTSBR), or (2) Training of Stationary Bicycle Riding without perturbations (TSBR). Both groups are trained in a sitting position by the same PerStBiRo system (see Figure 1) twice a week for 12 weeks, (i.e., details in regard to the magnitude and progression of the balance training is in the text (experimental and control group interventions) and Table 2. Compensatory (reactive) and anticipatory (proactive) balance control during standing and walking, functional balance, function, fear of falling, and aerobic endurance are measured pre-and post-training at the Schwartz Movement Analysis & Rehabilitation Laboratory in the Physical Therapy Department at the Faculty of Health Sciences at Ben-Gurion University of the Negev, Israel. The intervention is being provided inside participants' community centers or in their protected housing.

**Table 1 T1:** SPIRIT flow diagram of the effects of bicycle simulator training on balance control in older adults.

	**Enrolment**	**Allocation**	**Post-allocation**		
	***–T_**1**_***	**0**	***T_**1**_***	***Training measurement***	***T_**2**_***
**ENROLLMENT**					
**Eligibility screen**	X				
**Informed consent**	X				
**Questionnaires**Demographics, medical history, and past falls	X				
**Allocation**		X			
**INTERVENTIONS**					
***Experimental PerTSBR*** (12 weeks, twice a week)					
***Control TSBR*** (12 weeks, twice a week)					
**ASSESSMENTS**					
**Primary outcome measures**					
***Reactive balance control***—**Compensatory Step Execution tests during standing and walking** (single-step and multiple-step thresholds, first-step recovery initiation duration, first step duration, total balance recovery duration, total CoM displacement).			X		X
**Secondary outcome measures**					
***Balance postural control***—**Postural stability test**(traditional CoP sway and SDA parameters)			X		X
***Proactive balance control***—**Voluntary step execution test** (Reaction Time, Foot Contact Time, Preparation Time, Swing Time)			X		X
***Clinical functional balance***—BBS			X		X
***Aerobic capacity***—6MWT			X		X
**Questionnaires**MMSE, LLFDI, FES-I			X		X
**Performance monitoring during training:** ° Balance recovery (Experimental PerTSBR only) ° Cognitive dual task ° Bicycle resistance				X	

*Overview of time assessments and outcome measures. Pre-study personal interview (-T1); Pre-intervention baseline assessment (T1), Assessment during each of the 24 training sessions during 12-week interventions (Training measurement), Post-test assessment (T2)*.

**Table 2 T2:** Details of the PerTSBR intervention training program–the intensity and the progression levels.

**Training session (number)**	**Platform tilting (deg)**	**Platform peak Vel. (deg/sec)**	**Platform peak Acc. (deg/sec^**2**^)**	**Type of training (blocked/random)**	**Type of perturbations (internal, external)**	**Type of external cues (none, visual, sensorimotor)**	**Number of perturbations per minute**	**Pedaling intensity (bicycle resistance)**	**Cognitive task type and difficulty**
1	0°	Hands-free cycling practice				None	0	0	None
2	2°	10	10	Blocked Lt	External only	None	4	0	None
3	3°	20	20	Blocked Rt	External only	Visual	4	1	None
4	4–5°	25	25	Blocked Rt-Lt	External only	Visual	4	1	None
5	5–7°	30	30	Blocked Rt-Lt	Internal & External	Visual	4	1	None
6	5–8°	30	30	Blocked Rt-Lt	Internal & External	Sensorimotor	4	1	None
7	6–9°	30	30	Random	Internal & External	Sensorimotor	5	1	Find the odd one out of 1
8	5–10°	30	30	Random	Internal & External	Sensorimotor	5	1	Find the odd one out of 2
9	7–11°	30	30	Random	Internal & External	Sensorimotor	5	2	Find the odd one out of 3
10	8–12°	30	30	Random	Internal & External	Sensorimotor	5	2	Find a specific object 1
11	5–13°	30	30	Random	Internal & External	Sensorimotor	5	2	Find a specific object 2
12	5–13°	30	30	Random	Internal & External	None	6	2	Find the differences 1
13	9–14°	30	30	Random	Internal & External	Sensorimotor	5	2	Find the differences 1
14	10–15°	30	30	Random	Internal & External	Sensorimotor	5	2	Find the differences 2
15	5–16°	30	30	Random	Internal & External	Sensorimotor	5	2	Find the differences 2
16	5–16°	30	30	Random	Internal & External	None	6	3	Find the differences 3
17	11–17°	30	30	Random	Internal & External	Sensorimotor	5	3	Find the differences 3
18	12–18°	30	30	Random	Internal & External	Sensorimotor	5	3	Find the differences 4
19	5–19°	30	30	Random	Internal & External	Sensorimotor	5	3	Find the differences 4
20	5–19°	30	30	Random	Internal & External	None	6	3	Find the differences 5
21	13–20°	30	30	Random	Internal & External	Sensorimotor	5	3	Find the differences 5
22	14–20°	30	30	Random	Internal & External	Sensorimotor	5	3	Find the differences 5

*Details of the external perturbations, cognitive tasks, and bicycle resistance during the 22 potential training sessions. Deg, degrees; sec, seconds; sec^2^, second ^*^ second; Vel, velocity; Acc, acceleration*.

### Participants

A convenience sample of 68 community-dwelling older adults will be recruited (see sample size estimation below). Eligibility criteria are: 70 years of age or older, ability to walk independently without assistive devices, independence in daily living activities, and provision of a medical waiver signed by their primary care physician allowing participation in physical training that requires pedaling on a stationary bicycle two or three times a week. After completing a medical history questionnaire via an in-person interview at enrollment, volunteers are excluded if they suffer from: (a) ischemic heart disease which restricts exercise, (b) chronic obstructive pulmonary disease, (c) uncontrolled blood pressure, (d) severe vision problems (blindness), or (e) cognitive impairment, scoring <24 on the Mini-Mental State Examination. Further exclusion criteria include: (f) a period <1 year after hip or knee replacement surgery or after fractures of the lower extremities, (g) amputation of a lower limb, (h) neurological diseases or after a stroke, and (i) inability to ambulate independently, and/or (j) weight > 120 kg (exceeds safety harness weight limits). The study was approved by the Helsinki ethics committee at Barzilai Medical Center, Ashkelon, Israel (BARZI0104).

### Recruitment, Randomization, Group Allocation, and Blinding

Participants are recruited using advertisements, flyers, and personal contacts from community-dwelling centers and from several protected housing institutes in Beer-Sheva, Israel. They are assigned using randomization to one of the two intervention groups (PerTSBR or TSBR). The random allocation sequence is computer generated, and blocked randomization will ensure equal numbers allocated to each group. Group allocation is performed centrally by the principal investigator, who is involved in recruiting, scoring assessments, or administering the interventions (i.e., concealed allocation). Outcome measures will be obtained by two research assistants who are blinded to group allocation. Participants are not fully blinded to group allocation since they train on the same mechatronic device but without perturbations.

### Informed Consent

When an older adult is willing to participate in the study, a researcher approaches the subject, schedules a pre-study meeting to explain the study, and provides the study information sheet, information form for the primary care physician, and the permission to participate in the study/consent form. Participants are informed that this is a novel intervention method of a technology that aims to improve balance while riding a new stationary bicycle device, and that we hypothesize that they most likely will improve their function. In addition, they will be informed that both groups will perform bicycle training with or without perturbations thus, both are expected to improve function. To maintain the motivation of older adults to participate, they will be offered to participate in “other” exercise program after the training period. They are also informed that the training might be difficult in the beginning; thus, some muscle soreness will occur, and that participants are free to withdraw from the study at any time point, without consequence. Participants may also be withdrawn from the study due to changes in their health status that affect eligibility. A researcher will answer the participant's questions about the study, and participants may discuss the study with their family members, friends, or healthcare providers. All participants sign an informed consent statement via personal interview at enrollment. The informed consent process is documented by research personnel.

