### Data Collection and Outcome Measures

First, by personal interview with one of the researchers at the enrollment session (T1), each participant completes demographic, medical history, and past fall questionnaires (see Table 1). Then they undergo two assessment sessions: first at entry of the study (baseline assessment, T1), and the second at the end of the 12-week intervention period (T2). To ensure data quality, two research assessors blinded to group allocation and the training process receive training regarding data collection from the principal investigator and perform all measurements.

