### Sample Size Estimation

Sample size requirements were calculated using PS power calculation software (66). Because the aim of the study is to examine the effect of perturbation-based bicycle training on various aspects of balance control, well-known parameters that reflect reactive, proactive, and standing postural balance control were selected. Calculations were performed separately to determine sample size requirements based on a single-step threshold in standing (reactive balance), voluntary step execution (i.e., foot contact time) (proactive balance), and ML postural sway (standing postural control), all reflective of unsteadiness in balance control between older and younger adults (13, 14, 50, 55, 58, 67, 68) and between fallers and non-fallers (13, 15–21, 55–58, 60). Type I error probability of 0.05 and Type II error probability of 0.2 was applied for the three two-sided test calculations. Based on our preliminary results, the compensatory single-step threshold in standing was 10.8 cm of lateral translation in older adults with bicycle riding habits compared to 7.9 cm in age- and gender-matched controls [data in processing], the ML postural sway in EO was 30.6 mm in older adults with bicycle riding habits compared to 38.8 mm in controls (31), and the step execution times (i.e., foot contact time) in single-task condition of older bicyclists were 104 ms less than those of the controls (921 vs. 1,025 ms) (30). Using net reduction values (2.9 cm, 8.2 mm, and 104 ms, respectively) in combination with the initial variance estimates (standard deviations of 3.45 cm, 7.8 mm, and 134 ms, respectively), it was determined that 27 participants per group would be required. To account for reported attrition rates of about 25% in studies involving older adults (69), we decided to include about 34 participants in each group for a total of 54 (27 × 1.25 = 34).

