### Statistical Analysis

PASW Statistics version 26.0 are used for statistical calculations. Baseline characteristics are compared using independent *t*-tests and Mann–Whitney *U*-tests for continuous and ordinal variables, respectively. Descriptive data analysis and tests for the assumptions of normality (Shapiro-Wilk's statistic) are followed by a two-way repeated measure analysis of variance (ANOVA) for within subjects (pre- vs. post-tests) and between groups (experimental vs. control groups). The primary outcome variables are the single-step and multiple-step thresholds, the first-step recovery initiation duration, first step duration, total balance recovery duration, and the MoS. These variables were previously found to be able to distinguish between younger and older adults (14) and between fallers and non-fallers (15). The single-step threshold was previously shown to be an independent predictor of a future fall (16–21) and to reflect unsteadiness in reactive balance control among older adults with varying histories of falls (15). The secondary laboratory outcome variables are foot contact time (voluntary stepping), and the ML CoP sway, as well as SDA parameters (Cd and Ds). All these parameters were previously found to reflect unsteadiness in balance control (13, 50, 55, 56, 58, 67, 68) related to falls (13, 55–58, 60), and also related to older adults who have bicycle riding habits (30). The other secondary outcome measures are the BBS, 6MWT, LLFDI, and FES-I. An intention to treat analysis is conducted by carrying the last obtained measurements forward for those participants who do not complete all aspects of the study. The significance level is *p* < 0.05.

The effect size (ES) (Hedge's g) between the two independent groups is calculated by dividing the difference between the means of each group by the pooled baseline standard deviation of both groups. Values between 0.2 and 0.49 are considered small, between 0.5 and 0.79 moderate, and 0.8 and higher is considered a large effect. In addition, for each outcome parameter, we explore whether a minimal detectable change has been reached. As data will be analyzed at the end of the study, there is no plan for interim analyses of primary and/or secondary variables.

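### Withdrawal from the study on loss of eligibility, combined with carry-forward from baseline, creates avoidable outcome-related missing data at T2

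*Protocol article*

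**What the plan says.** The Informed Consent section gives participants their own right to leave ("participants are free to withdraw from the study at any time point, without consequence") and then adds a second route: "Participants may also be withdrawn from the study due to changes in their health status that affect eligibility". What ends is participation in the study. The sentence does not say who decides, when, or whether T2 is still measured.

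Eligibility is set out under Participants and screened at enrolment, before allocation (Table 1). Some exclusion criteria can newly arise during 12 weeks of training. Examples are "a period <1 year after hip or knee replacement surgery or after fractures of the lower extremities", a stroke, uncontrolled blood pressure, and loss of independent walking.

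Under Data Collection and Outcome Measures there are two assessment sessions, T1 at baseline and T2 at the end of the 12-week intervention. Table 1 shows no trial outcome between them, only performance monitoring during training.

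On non-completers, Statistical Analysis says: "An intention to treat analysis is conducted by carrying the last obtained measurements forward for those participants who do not complete".

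**The concern.** Each provision is ordinary alone; the difficulty lies in the combination. A health change large enough to affect eligibility is likely to be related to balance and walking, which the trial measures. If such a change ends study participation, T2 is not obtained. The last value available is then T1, and carrying it forward records no change for someone who may have become clearly worse. The withdrawal rule creates the missing value and the analysis rule hides the deterioration. A different imputation method could not restore a measurement that was never sought.

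At stake is the arm comparison. Only the experimental arm is perturbed, and the Weaknesses section itself warns that the training is challenging and may cause drop-out, so unequal withdrawal is possible. With 27 evaluable participants required per arm, a few such cases carry some weight.

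**Working it through.** **Planning figures (Sample Size Estimation).** Two-sided alpha 0.05 and power 0.80, with n per arm = 2 × (1.960 + 0.842)² × (SD/difference)²:

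- Single-step threshold, 2.9 cm and SD 3.45 cm: 22.2, so 23.
- ML sway, 8.2 mm and SD 7.8 mm: 14.2, so 15.
- Foot contact time, 104 ms and SD 134 ms: 26.1, so 27.

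The largest reproduces the stated 27, and 27 × 1.25 = 33.75 gives the stated 34. These figures only set the scale. The foot contact planning effect is d = 104/134 = 0.776 SD.

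**What carry-forward does.** With only T1 and T2, a participant without T2 is scored T2 = T1, a change of 0. Let a fraction wE of the experimental arm and wC of the control arm be withdrawn. Score changes so that positive means better.

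**Illustration A: withdrawn participants are k SD worse than completers of their own arm.** Assumptions not in the protocol: wE = 3/34 = 0.088, wC = 1/34 = 0.029, k = 1 to 2, and no change in control completers.

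- True contrast over all randomised = d - k(wE - wC). For k = 1: 0.776 - 0.059 = 0.717. For k = 2: 0.776 - 0.118 = 0.658.
- Carried-forward contrast = (1 - wE) × d = 0.912 × 0.776 = 0.708.
- Bias = k(wE - wC) - wE × d. For k = 1: 0.708 - 0.717 = -0.01 SD. For k = 2: 0.708 - 0.658 = +0.05 SD.

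This is about -1% to +6% of 0.776. The sign changes at k = d × wE/(wE - wC) = 0.776 × 3/2 = 1.16 SD. At k = 1 the three experimental withdrawals have truly changed by 0.776 - 1 = -0.224 SD each and the one control withdrawal by -1 SD. Scoring all four as zero helps the control arm slightly more (1/34 = 0.029 against 3 × 0.224/34 = 0.020). If control completers improve by c, the bias falls by a further c(wE - wC).

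**Illustration B: withdrawn participants decline by L from baseline, in the same way in both arms.** Single-step threshold, assuming +2.9 cm in experimental completers and 0 in control completers. Here bias = L(wE - wC).

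| wE | wC | L (cm) | True (cm) | Carried forward (cm) | Bias (cm) |
|---|---|---|---|---|---|
| 25% | 25% | 1.45 or 2.9 | 2.18 | 2.18 | 0 |
| 10% | 10% | 1.45 or 2.9 | 2.61 | 2.61 | 0 |
| 25% | 10% | 1.45 | 1.96 | 2.18 | +0.22 |
| 25% | 10% | 2.9 | 1.74 | 2.18 | +0.44 |
| 10% | 25% | 1.45 | 2.83 | 2.61 | -0.22 |
| 10% | 25% | 2.9 | 3.05 | 2.61 | -0.44 |

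The 25% is the protocol's allowance for attrition from all causes, so attributing all of it to this rule in one arm is an extreme case.

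**The case against.** A reader might infer that the withdrawal provision contradicts the intention-to-treat plan. It does not. Statistical Analysis keeps non-completers in the analysis by carry-forward, so nobody leaves the analysis set.

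A reader might also infer that harmed or deteriorating participants do leave before T2, or that unblinded staff choose who is measured. The text is permissive, mentions neither harm nor T2, and names no decision-maker. It sits among what participants are told at consent. Harm cases are not lost either, since the Adverse Events section has all adverse events collected.

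A third tempting reading is that the contrast is inflated by (3/34 - 1/34) × 1 to 2 SD = 0.06 to 0.12 SD. That is the bias of an analysis of completers only. Under the planned carry-forward the same assumptions give -0.01 to +0.05 SD. Nothing in the protocol supports a 3 to 1 imbalance: Data Monitoring reports very mild events in the team's previous studies, with similar frequency and severity in perturbation and control groups.

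Finally, health-related withdrawal clauses are common, and follow-up after stopping training is often left to the full protocol. That lowers the weight of the point but does not remove it, because this article states a rule, withdrawal from the study, and the concern rests on that rule and the stated carry-forward. It is also fair that someone with a recent fracture might not be testable on the primary outcomes whatever the wording.

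**Conclusion.** The point holds as a modest, cheaply removed weakness. The protocol permits withdrawal from the study after randomisation for health changes that affect eligibility. With two assessments and carry-forward, a participant withdrawn before T2 is scored as having zero change, whatever happened to them. Bias needs withdrawals or declines to differ between arms; with both balanced, Illustration B gives zero. The protocol determines neither sign nor size. Illustration A gives about -0.01 to +0.05 SD on assumed withdrawals of 3/34 and 1/34. Illustration B gives up to 0.44 cm in either direction (15% of 2.9 cm) on a much larger assumed imbalance. The case for change is avoidable missing data related to outcome, not a demonstrated bias in favour of the experimental arm.

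**What to change.** Reword the sentence under Informed Consent so that a health change affecting eligibility leads to an investigator decision on whether training continues, while the participant remains in the study. Invite that participant to T2 for every planned assessment judged safe: the primary stepping tests where possible, and otherwise at least the LLFDI and FES-I. State that entry criteria are not re-applied after randomisation to end follow-up, and that the participant's own right to withdraw is unaffected. Report withdrawals from training and from the study separately, with reasons, by arm.

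The cost is about one paragraph and a few extra T2 contacts, using assessments already planned. The change will not recover everything: participants who cannot safely be tested will still lack primary-outcome data.
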